#### Secondary outcome measure

• The Dementia Quality of Life Instrument (DQoL) is a 30-item self-assessment. 5 subscales and one global item are assessed with a five-point-Likert-scale: *positive affect *(6 items), *negative affect *(11 items), *feelings of belonging *(3 items), *self-esteem *(4 items), and *sense of aesthetics *(5 items). The ranges of scores differ from scale to scale (from 5-15 to 5-55). Higher scores indicate better quality of life, except in the subscale *negative affect*. The DQoL was developed specifically to be completed by people with dementia. The development process included consultation with people with dementia, caregivers, and professional care providers. In an American sample, 96% of 99 people with dementia (MMSE > = 13) were able to respond to questions appropriately [46]. This study revealed moderate to high internal consistency (.67 - .89) and a good two-week test-retest reliability (.64 - .90). There were no significant differences between patient groups with mild (MMSE > 17) and moderate (MMSE < = 17) dementia severity in terms of scale reliability. Correlation of DQol subscales and the Geriatric Depression Scale ranged from -.42 to -.64. A Japanese study replicated similar results for understanding, internal consistency and convergent validity at baseline and in a one year follow up. The sample consisted of 72 people with dementia with MMSE score > = 13 [47,48]. In a British study on longitudinal change in quality of life, 60% of people with a MMSE of 10 could complete the DQoL [49]. In an American study with 67 patients diagnosed with mild cognitive impairment or mild Alzheimer's disease, a three-factor solution emerged reliably from factor analyses corresponding to positive affect, negative affect and aesthetics. This DQoL factor structure was nearly identical between ratings of patient and caregiver [50]. Within the WHEDA study, the DQoL is applied to primary caregivers as self-assessment. With the patients, it is performed as an interview, in order to ensure the validity of rating. Patients are asked to answer three screening questions and data will not be collected, if more than one answer is missing.

• The SF-12 is the reduced version of the SF-36, a generic self-assessment evaluating health status and disability. The instrument generates a mental and a physical component summary score from 12 weighted items with response categories varying from dichotomous, to six-point scales using a complex algorithm based on norm data of a major American sample. Higher scores indicate better health status. Metric properties are excellent [51] and German norm data are available [52]. The instrument supports the calculation of Quality Adjusted Life Years (QALY). The SF-12 has been applied to people with dementia recently [53] and to caregivers [54]. The SF-12 appears to identify under-reported mental health problems in dementia caregivers [54]. In addition, this assessment tool seems to be appropriate for the evaluation of health-related quality of life from both the caregiver's and the patient's perspective. Arlt and colleagues [53] found that family caregivers tend to rate the patient's health-related quality of life lower than the person with dementia him/herself. For that reason the SF-12 is applied in the WHEDA-study to both the caregiver and the patient. In order to ensure quality of patients' data, the WHEDA-assessor applies the SF-12 as an interview to the patient and checks his/her understanding by means of the DQoL screening questions.

• In the Sense of Competence Questionnaire (SCQ [55]), caregivers rate their agreement with 27 statements on the experience of caregiving on a five-point-Likert-scale (from *agree very strongly *to *disagree very strongly*). The SCQ records three domains: *Consequences of involvement in care for the personal life of the caregiver *(8 items), *satisfaction with one's own performance as a caregiver *(12 items) and *satisfaction with the person with dementia as a recipient of care *(7 items). Scores range from 27 to 135 (higher scores denote a greater sense of competence). The three domains of the SCQ and its internal consistency are confirmed in validation studies involving people with stroke and dementia (variance explained by three factors: 49% respective 42%, Cronbach's alpha: .68 - .77, .83 - .85 respectively [56,57].

• The Center for Epidemiologic Depression Scale (CES-D) [58] is frequently used to evaluate mood and depression levels of persons caring for patients with dementia [27,59-62]. Caregivers rate the occurrence of 20 symptoms on a four-point Likert Scale (from *seldom *to *mostly*). Scores range from 0-60, lower scores indicate less depressive indicators. Robust metric properties of the CES-D are established [63]. Correlations with Hamilton Depression Scale and Becks Depression Inventory are moderate to high (.49 to .94). Sensitivity to change in individuals within samples treated with anti-depressive drugs was significant (.0001 to .0004). Cronbach's alpha of .89 indicates high internal consistency. In the WHEDA study, the CES-D is applied as self-assessment.

• With the Cornell Scale for Depression in Dementia (CSDD), the caregiver rates 19 symptoms of the patient within four domains: (1) *mood and related signs *(2) *behavioural disturbance *(3) *cyclic function and ideational disturbance *and (4) *physical signs *[64]. All 19 symptoms are rated on a three-point continuum: 'absent', 'mild or intermittent' or 'severe'. Scores range from 0-38, lower scores indicate less depressive characteristics, nine or more points indicate a depressive disorder. Müller-Thompsen et al. [65] found significant high correlations between the CSDD and three other scales for depression in a sample of patients with mild Alzheimer Disease (Geriatric Depression Scale: .70; Montgomery and Åsperg Depression Scale: .93; Nurses Observation Scale for Geriatric Patients, Mood: .72) and high correlations with the Montgomery and Åsperg Depression Scale (.74) in the more severely impaired group. Cronbach's alpha of .81 and .82 indicated high internal consistency in both, the mild and severe dementia group. The validation study of Korner and colleagues [66] revealed high inter-rater reliability for a sub-sample of 15 people with dementia videotaped and rated by independent raters (ICC: .84). Lam et al. [67] compared four depression scales in 88 elderly outpatients with dementia. They found different cut-off values for sensitivity and specificity of the CSDD in subgroups of patients with mild (91.7%, 80% respectively, cut off 6/7) and moderate to severe dementia (70%, 87% respectively, cut off 12/13).

• The primary caregiver provides data on his/her own and the patient's resource utilization in a self- and proxy-report (adapted Resource Utilization in Dementia RUD [68]). The adapted RUD records resource utilization in the following fields:

 a. Medical care for the patient: (1) periods of illness, nights in hospital or nursing home, number of consultations and purchase of technical aids within the last six weeks. (2) Number and duration of therapy sessions (such as physical or psychotherapy), nursing care or home care and visits to day care groups within the last two weeks;

 b. Informal care for the patient: (1) Hours per day of the primary caregiver for assistance in activities of daily living, instrumental activities of daily living and supervision; and also hours per day the patient is without supervision. (2) Hours of supervision by others, informal or professional caregivers within the last two weeks (as recommended by Neubauer et al. [69]);

 c. Medication of the patient within the last two weeks;

 d. Medical care for the caregiver: (1) periods of illness, nights in hospital or nursing home, number of consultations and purchase of technical aids within the last six weeks. (2) Number and duration of therapy sessions, nursing care or home care, visits to groups for caregivers of people with dementia within the last two weeks;

 e. Amount of work per week and days absence from work of the primary caregiver;

 f. Medication taken by the primary caregiver within the last two weeks.

Wimo and Nordberg [70] found fair to high correlations between times of caregiving as observed by a special team and estimated in RUD by the caregivers in twenty institutionalized persons with dementia (correlation coefficients in ADL-time .81, *p *< .001; in IADL .29, *p *= .03; supervision .51, *p *< .001). In the WHEDA-study, the adapted RUD is applied at every measurement time point after recruitment, in order to record the full resource utilization until the one year follow up. For supporting the retrospective data collection, the caregiver keeps a diary of periods of illness, nights in hospital or nursing home, number of consultations and purchase of technical aids.

• Patient and caregiver rate their satisfaction with experimental and control treatment on a five-point Likert scale on five items: How (1) patient, (2) sympathetic and (3) encouraging was the therapist? How much did the treatment deal (4) with your everyday life and (5) goals that are important to you? How satisfied are you in general with the treatment? The questionnaire also asks for comments and suggestions.

#### Control measures

• The Sociodemographic Questionnaire provides data on the patient's and primary caregiver's age, sex, socio-economic and educational status, relation between patient and caregiver and their housing. It is a self- and proxy-report of the primary caregiver.

• The study physician evaluates the patient's cognitive status using the Mini Mental State Examination, a broadly applied performance test with established metric properties [32]. The MMSE ranges from 0 to 30. The higher the score the better the cognitive status.

• The Geriatric Depression Scale (GDS [71]) is a self-rating scale consisting of 30 questions to be answered dichotomously as 'yes' and 'no'. The GDS score ranges from 0 to 30; higher scores indicate major depressive indicators. The cut-off point for depression is 12. Correlation of GDS and CSDD scores was .70 in a German sample of 140 patients with mild dementia [65]. The authors found sufficient internal consistency in subgroups of patients with mild (MMSE ≥ 18) and moderate to severe (MMSE<18) dementia (Cronbach's alpha: .83, .74 respectively).

#### Process measures

• Problems during treatment and adherence to the manuals are recorded by an evaluation form for every treatment case in both study groups.

• The study therapists evaluate their adherence to the study protocol as well as barriers and facilitators of the treatment process within a self-report questionnaire for the relevant period (seminar, pilot phase, treatment series). In addition, this questionnaire collects the therapists' ratings and comments on the adherence of patients and caregivers to therapeutic recommendations (interventions group only, since follow up visits are missing in control group and control for adherence is not possible). The summarised self-report results are reflected in a focus group discussion for all therapists involved in the study.

• Further indicators of adherence to protocol are the numbers of treatments, assessments and medical control visits inside, versus outside, the protocol schedule. Additionally, the completeness of measurements at every time point is evaluated (eg. videotape or patient interview might be missing due to reduced cognitive capacity).

### Sample size

Although the Dutch original randomised control trial [26] found very large effect sizes on the performance scale of the Interview of Deterioration in Daily Living Activities in Dementia (at 12 weeks follow-up d-value = 2.4), the power of the WHEDA-study is calculated conservatively in order to detect small effects. The rationale is the change in design; that there is an active control treatment, less professional experience in the experimental treatment in Germany, less patients per therapist and a longer follow-up in a sample with expected progress in dementia, may reduce the expected effects. The power calculation is based on an analysis of variance of two groups and four measurement time points (since in the postal follow up at 52 weeks the IDDD is recorded, too). Hypothesising an alpha of .05 (two-sided), a power of .80 and a correlation of .7 between four measurement time points, a sample of 84 persons is needed, in order to detect an effect of f = .10 [72]. According to drop out rates of the Dutch study, 280 patients must be screened and 140 recruited (see figure 1).

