### Outcomes

The primary endpoint is the comparison between the intervention group and control group in the change in daily functioning from baseline to follow-up as indicated by the Interview for Deterioration in Daily Living Activities in Dementia (IDDD) over three post intervention time points. The WHEDA measurement scheme with dependent variables and measurement instruments is provided in table 1. The primary and most secondary outcomes are oriented to patient and caregiver. Daily functioning, quality of life, mood and daily interaction are directly related to individual everyday life and represent the user's perspective in most self- and proxy-assessments used in the WHEDA study. It is of great importance to know how long a therapeutic approach may stabilise daily functioning after the intervention is finished. The cognitive decline in dementia is a strain on patients and caregivers. Its progress varies, but major and consistent changes are mostly not observable before a half year progress of disease. Consequently, the follow-up assessments are appointed at week 16 and 26 after baseline. In order to justify a potential implementation in practice, service providers as well as political and economical decision-makers within the health care system need trustworthy evidence about an innovative intervention. Hence feasibility, acceptance and costs of active and control treatment are additional outcomes of the WHEDA study.

**Table 1 T1:** WHEDA measurement scheme

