**Primary outcome**												
Patients' functioning in everyday life	IDDD, PRPP-Video rating		X	X		X		X				

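### The 84 is computed correctly, but for a group-by-time interaction in which f = .10 is about half a standard deviation, not a small effect; the week-52 reason given for the four time points contradicts Table 1

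*Protocol article*

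**What the plan says.** The Sample size section sets the inputs as "Hypothesising an alpha of .05 (two-sided), a power of .80 and a correlation of .7 between four measurement time points", for an analysis of variance with two groups, and concludes that "a sample of 84 persons is needed, in order to detect an effect of f = .10". It describes the power as "calculated conservatively in order to detect small effects". The reasons given are an active control, less experienced therapists, fewer patients per therapist and a longer follow-up, all of which may shrink the very large Dutch effect (d = 2.4). The Discussion repeats that the power was conservative. The recruitment target is 140.

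The section does not say which ANOVA term is tested, and it gives no effect in SD units or IDDD points. It explains the four time points by adding "since in the postal follow up at 52 weeks the IDDD is recorded, too". In Table 1 the primary outcome row ("IDDD, PRPP-Video rating") has crosses at weeks 0, 6, 16 and 26 only. The Outcomes section defines the endpoint as change in IDDD from baseline "over three post intervention time points". Statistical methods plans a repeated-measures ANOVA with two groups and four time points, without listing them.

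**The concern.** Cohen's f has a different meaning for each term of a repeated-measures ANOVA. By convention f = .10 is labelled small, and for a two-group main effect it equals d = .20. A reader told that 84 patients suffice for small effects will therefore think of a difference of about a fifth of an SD. If 84 comes from another term, that reading is wrong, and a null result could be taken as ruling out small benefits that the trial had little chance of detecting.

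The second issue is which occasions enter the powered analysis. The stated reason for having four relies on a measurement that the schedule does not contain.

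**Working it through.** **Inputs** (Sample size section; 1:1 allocation from Randomisation): k = 2 groups, m = 4 occasions, ρ = .7, f = .10, two-sided α = .05, power .80. Assumed: sphericity, equal correlations, no true group difference at baseline.

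**1. Reproduce the 84.** Group-by-time interaction: λ = f²·N·m/(1 − ρ), df₁ = (k − 1)(m − 1) = 3, df₂ = (N − k)(m − 1).
- N = 84: λ = .01 × 84 × 4/.3 = 11.2, df = 3 and 246, power .805.
- N = 82: power .794.

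So 84 is the smallest even total that reaches 80%. The multivariate form of the same test gives 86.

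**2. Try the group main effect.** λ = f²·N·m/(1 + (m − 1)ρ), with 1 + 3 × .7 = 3.1, df = 1 and N − 2.
- N = 84: λ = .01 × 84 × 4/3.1 = 1.08, power .177.
- 80% power needs N = 612.

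The time effect has the same λ and df as the interaction and also returns 84, but it does not compare treatments.

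**3. Translate f = .10 in the interaction into a group difference.** With δⱼ the standardised group difference at occasion j, f² = Σ(δⱼ − δ̄)²/(4m).
- Constant benefit (0, d, d, d): δ̄ = .75d; the sum is (.5625 + 3 × .0625)d² = .75d²; f = d·√(.75/16) = .2165d; d = .10/.2165 = **.46**.
- Linear in calendar weeks 0, 6, 16, 26 (0, .231, .615, 1 times d): δ̄ = .4615d; the sum is .580d²; f = .190d; d at week 26 = **.53**. Linear in visit number instead gives .54.
- Other patterns: (0, 0, d, d) gives .40; (0, d/2, d, d) gives .48; (0, d/2, d/2, d) gives .57.

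**4. Power for a difference that is small in the usual sense.** For a constant d = .20, f = .2165 × .20 = .043.

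| Analysed | Power of the interaction at constant d = .20 | Constant d detectable with 80% power |
|---|---|---|
| 84 | 20% | .46 |
| 140 (no loss) | 31% | .355 |

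80% power at d = .20 would need 438.

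**5. Time points.** Baseline plus three post-intervention visits is four, which matches the crosses in Table 1, the endpoint and Statistical methods. Adding a week-52 IDDD would make five occasions, for which the same formula gives 74 rather than 84. The stated 84 therefore fits four occasions, and the week-52 remark does not explain them.

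**6. A 1-df alternative, for comparison.** For the baseline-adjusted mean of weeks 6, 16 and 26, the variance in SD² units is (1 + 2 × .7)/3 − .7² = .80 − .49 = .31. With N = 84, SE = √(.31 × 4/84) = .1215. By the noncentral t, 80% power is reached at d ≈ .345 with 84 and ≈ .27 with 140. At d = .20 power is 37% and 56%; at d = .46 with 84 it is 96%.

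**The case against.** Several points on the other side stand. The sample size is not miscalculated. The label small for f = .10 is the conventional one. Set against the Dutch d of 2.4, planning for .46 is planning for about a fifth of that effect (.46/2.4 = .19), so the calculation is cautious relative to that trial. The intention-to-treat analysis takes everyone with valid data, so the analysed number may exceed 84. What this does not rescue is the claim about small effects: even with all 140 analysed, power at a constant d = .20 is 31%.

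A reader might infer two stronger points that the article does not support. The first is that the count of four conflicts with Table 1 and the endpoint. It does not; only the parenthetical reason conflicts. Nothing defines the four as weeks 6, 16, 26 and 52, so the consequences of that set are conjecture. The week-52 gap is also unlikely to be a text-extraction fault, because other rows of Table 1 keep their week-52 crosses.

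The second is that the omnibus interaction is the wrong test for the endpoint. The Outcomes section does not say that the three post-intervention visits are averaged, and with baseline among the occasions a group-by-time test is a conventional test of differential change. It is less efficient than a single averaged contrast when the benefit is steady, but it does not contradict the endpoint.

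**Conclusion.** The concern holds as a fault in the claim attached to the sample size, not in its arithmetic. The 84 is the number for the 3-df group-by-time interaction, where f = .10 is a group difference of about .46 SD (constant) or .53 SD at week 26 (linear), and about .40 to .57 across the patterns tried. The statement that the trial is powered for small effects is therefore not supported. The conclusion rests on ρ = .7, sphericity and no baseline difference. The size of d depends on the assumed pattern over time, but no pattern tried comes near .20.

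The contradiction over week 52 is real but narrow: the Sample size section says that the IDDD is recorded then, and Table 1 does not schedule it.

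**What to change.** 1. Name the tested term in both Sample size and Statistical methods: the group-by-time interaction over weeks 0, 6, 16 and 26.
2. Restate the power as 80% for a constant post-baseline difference of about d = .46 with 84 analysed (about .355 with 140), and remove the reference to small effects. If calling the calculation conservative is kept, say that this is relative to the Dutch effect.
3. Reconcile week 52: either delete the parenthesis, or add the IDDD to Table 1 at week 52 as a secondary time point outside the powered analysis.

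These are changes of wording and schedule and need no more patients.

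Optional: make the primary test the 1-df group difference in the baseline-adjusted mean over weeks 6, 16 and 26, with per-visit estimates as secondary. This lowers the effect detectable with 80% power to about d = .345 with 84 and .27 with 140. The cost is somewhat less sensitivity to an effect present at one visit only. Since recruitment is described as finished, such a change would have to be documented before outcomes are seen by group.

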**Figure 1 F1:**
[figure not shown]
**WHEDA flow chart (planned progress)**.

### Randomisation

After the recruitment of an individual, the physician of the study centre e-mailed the request of randomisation to a statistician at a distant site. The physician also informed the assessor (and optionally a co-ordinator of the study centre) and asked him/her to schedule all assessment dates according to the protocol. After the referral by the centre physician, the independent statistician allocated the individual to COTP or COTC. The randomisation sequence was computer-generated with blocking by centre and groups of two persons, without stratification and in a ratio of 1:1. Group allocation was e-mailed to the therapists at the study centre. The therapists decided who would be responsible for this case and the lead therapist confirmed reception of group allocation to the independent statistician. In addition, the lead therapist informed his centre team that he had received group allocation. In order to avoid any contamination, the centre therapists must schedule treatment sessions on their own. He/she also has to fax the records to the WHEDA-headquarters and retain their records, strictly separated from any other centre staff. Masking of patients and caregivers is not possible due to the different quantity of home visits between intervention and control group. Assessors might be contaminated by hints of patients or caregivers during the assessments at home. Assessors, patients and caregivers are asked to avoid any talks about the treatment. The extent of assessor 'blinding' will be evaluated by the comparison of actual group assignment and the assessor's estimation of group assignment. The procedure of video-rating ensures the full 'blinding' of the Dutch raters of an individual's assignment to group. Independent staff of the WHEDA-headquarters check and 'clean' the videotapes from any hint of group assignment or personal data, before the tapes are transferred to the Netherlands.

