### Statistical methods

Data are entered via special MS Access entry masks automatically controlling for data plausibility. In addition, sections of entered data are checked for typing errors by hand, in order to ensure an error rate lower than 0.2%. Baseline measures and demographics of participants significantly differing at baseline in intervention and control group and control measures are used as co-variates in an analysis of variance with repeated measures with two groups and four measurement time points. If the diagnosis of extent and type of missing data reveal that the precondition is given, the Full Information Maximum Likelihood (FIML) method will be applied for data replacement [73]. The primary intention-to-treat analysis, including all participants with valid data (whether they did or did not receive the intervention), will be compared with a per protocol analysis excluding all participants with documented deviations from the protocol (ie. not receiving the entire intervention or receiving an incomplete follow-up). The comparison of these groups will be adjusted for baseline imbalance and process variations. Variations in the adherence to protocol; to the treatment manual and to therapeutic recommendations; variations in medication and progress of cognitive decline as well as variations in the quality of supporting or hindering structures and processes at the study sites are considered as possible mediators. All statistical tests will be two-sided on an alpha level of .05.

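### Allocation in pairs within centre is stratification by centre, but the text denies it and the primary model omits centre; fixed pairs also let one leaked arm reveal a second

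*Protocol article*

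**What the plan says.** On the scheme, the Randomisation section of the protocol article says: "The randomisation sequence was computer-generated with blocking by centre and groups of two persons, without stratification and in a ratio of 1:1".

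On who learns what, the same section says that after recruitment "the physician of the study centre e-mailed the request of randomisation to a statistician at a distant site". The arm then goes to the therapists: "Group allocation was e-mailed to the therapists at the study centre". For everyone else, "the lead therapist informed his centre team that he had received group allocation", and therapists must "retain their records, strictly separated from any other centre staff". The physician also tells the assessor about each recruited patient so that visits can be booked. Patients and caregivers are open: "Masking of patients and caregivers is not possible due to the different quantity of home visits between intervention and control group". The section concedes that "Assessors might be contaminated by hints of patients or caregivers during the assessments at home", and it plans to compare assessors' guesses with the true assignment.

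On analysis, Statistical methods specifies "an analysis of variance with repeated measures with two groups and four measurement time points". The covariates are baseline measures and demographics that differ significantly between the arms, plus the control measures. Table 1 lists those as demographics, depression, cognition, medication and periods of illness. Site structures and processes enter only as possible mediators. The Discussion adds that adjusted analyses will consider variation in settings.

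**The concern.** There are three linked problems.

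- **Description.** A sequence with its own blocks in each centre is stratified by centre. A statement in the same sentence that there is no stratification may lead whoever programs the analysis to treat the design as unstratified.
- **Model.** The analysis should reflect the groups within which patients were randomised. The seven centres differ by design (university memory clinics, a municipal hospital, a private practice). If outcomes differ between centres and centre is not in the model, that variation goes into the error term although the randomisation has already balanced it.
- **Predictability.** With fixed pairs, the arm of one member fixes the arm of the other. In a trial with open patients and acknowledged hints to assessors, one piece of information can unblind two patients.

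**Working it through.** **1. Which test was the trial sized for?** Inputs from Sample size: f = 0.10, two-sided alpha 0.05, power 0.80, correlation 0.7, two groups, four time points, N = 84.

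- Group-by-time test: λ = f²·N·m/(1 − ρ) = 0.01 × 84 × 4/0.3 = 11.2, with df 3 and (84 − 2) × 3 = 246. Power is 0.805, and 84 is the smallest even N that reaches 0.80.
- Between-group test of level: λ = f²·N·m/[1 + (m − 1)ρ] = 0.01 × 84 × 4/3.1 = 1.08. Power is 0.177, and 0.80 would need N = 612.

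The stated 84 therefore reproduces only as a group-by-time test. This agrees with Outcomes, which defines the primary endpoint as a comparison of change from baseline.

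**2. Can the covariate rule pick up centre?** Pair blocks hold the difference in arm sizes to at most one patient per centre. Centre therefore cannot differ significantly between arms, and it is not among the control measures. The rule excludes the one factor used in allocation.

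**3. What does omitting centre cost?** The documents give no centre variance, so the shares below are assumptions. Simulation: 7 centres × 20 patients (equal sizes assumed), pair blocks, total variance 1, correlation 0.7, true difference 0.3 SD. There were 8,000 runs for alpha and 4,000 for power. Simulation error is about √(0.05 × 0.95/8000) = 0.002 for alpha and √(0.8 × 0.2/4000) = 0.006 for power.

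Test of level (mean of the three post-treatment values), no centre-by-time variation:

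| Centre share | Alpha, centre out | Power, centre out | Power, centre in |
|---|---|---|---|
| 0% | 0.051 | 0.503 | 0.504 |
| 5% | 0.045 | 0.513 | 0.530 |
| 10% | 0.040 | 0.513 | 0.562 |
| 20% | 0.027 | 0.529 | 0.623 |

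Test of change (post-treatment mean minus baseline):

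| Centre share | Centre-by-time share | Power, centre out | Power, centre in |
|---|---|---|---|
| 5% | 0% | 0.799 | 0.799 |
| 10% | 0% | 0.796 | 0.796 |
| 20% | 0% | 0.790 | 0.789 |
| 5% | 2% | 0.801 | 0.817 |
| 10% | 5% | 0.827 | 0.859 |

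A constant centre effect enters the baseline and later values equally and is subtracted out. Only differences in time course remain. In the last row, alpha for the change test is 0.031 without centre and 0.046 with it, so that error is also conservative.

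**4. Predictability.** In a pair, the first arm is a 50:50 guess and the second is certain. The share that is certain is 1/2, or 70 of 140 if all pairs are complete. The expected rate of correct guesses is (0.5 + 1)/2 = 75%. By exact enumeration, fixed blocks of four give 33% certain and 71% correct. All these figures presuppose a guesser who knows the block size and the earlier arms.

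**The case against.** The strongest reply has five parts.

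- **Wording.** The sentence itself discloses blocking by centre, so the denial of stratification may mean only that no further factors were used. That is a fair reading of the intent, but it is not what the sentence says.
- **Model.** This is a condensed article, and an analysis plan that is not shown could add centre. Adjusted analyses for settings are also foreseen. This stands to the extent that a reader should not infer that site differences are ignored altogether. But the article does list the model's terms and its covariate rule, and neither admits centre. A mediator analysis is not adjustment of the primary test.
- **Magnitude.** A reader might apply 1/√(1 − share) and infer that assumed centre shares of 5–10% inflate the primary standard error by 2.6–5.4%, equivalent to losing 7–14 of 140 patients. That formula describes comparisons of level. The primary endpoint is change, where a constant centre effect cancels, so these figures do not apply to it.
- **Concealment.** A reader might infer that half the allocations were known to those enrolling. The documents do not support this. A distant statistician allocates on request, the physician and assessor are not sent the arm, therapists' records are kept apart, and nothing says that sites knew the block size.
- **Route to the outcome.** The IDDD is the caregiver's own rating, and caregivers are open whatever the block size. The PRPP is scored by external raters from cleaned tapes. This limits the effect on both primary measures. Assessors still interview patients and initiate and film the PRPP activities, so some risk remains.

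**Conclusion.** The point holds, as an improvement to the description and analysis rather than a threat to validity. The scheme is stratified by centre and misdescribed, and the stated model omits that factor under a covariate rule that cannot restore it.

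For tests of level, the omission makes the test conservative and costs power: 0.02 to 0.09 in the simulation at assumed centre shares of 5% to 20%. For the change or group-by-time test, the loss is nil unless centres differ in time course. It is then about 0.03 (0.827 against 0.859) at an assumed 5% centre-by-time share. The error is on the conservative side, so it gives no reason to doubt a positive result. N = 84 is unaffected.

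The figure of 70 in 140 certain allocations is exact for complete pairs, but conditional on knowing the block size and the first arm. Therapists receive every arm and can deduce the second directly, though they are not described as enrolling patients. For the physician or assessor it takes a leak. The article concedes that hints from patients or caregivers are possible, and the assessor hears of each recruited patient and so could work out the enrolment order. Whether any leak occurred cannot be told from the document.

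**What to change.** - **Description.** State that allocation was blocked within centre in pairs, and so stratified by centre, with no further factors if that is what was meant. Report who knew the block size. Cost: two sentences.
- **Model.** Add centre as a fixed factor to the primary model. Cost: 7 − 1 = 6 degrees of freedom, for example from 138 to 132 in a two-group comparison of 140 patients. Add centre-by-time if centres differ in time course; with four time points this takes (7 − 1) × (4 − 1) = 18 within-patient degrees of freedom.
- **Checks on data already collected.** Tabulate the planned assessor guesses by position in the pair. Compare baseline IDDD and MMSE between first and second pair members, by arm. A higher share of correct guesses, or a difference in baseline between the arms, that appears only among second members would point to use of the pairing. Cost: one table.

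Changing the block size is no longer useful, because the Recruitment section gives the recruitment period as August 2008 to April 2009.
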